### Sampling method

TB patients under the DOTS strategy who fulfil the inclusion and exclusion criteria will be recruited and randomised into the control and intervention groups. The participants will be selected using a simple random sampling technique.

### Data collection

#### Cluster randomized trial flow

*Participant recruitment*. The researcher will inform the respiratory specialist and medical doctors in tuberculosis (TB) clinics about the study objectives and the eligibility criteria to facilitate patient selection for the randomised controlled trial (RCT). After the TB patients complete their appointment with the physician in the respiratory clinic, the nurse will direct the TB patients who fulfil the inclusion criteria to the researcher. The researcher then explains the purpose and benefits of this study. TB patients who agree to join will be asked to complete a written consent form to the relevant authority in Abu Anga hospital before they are asked to answer the questionnaire. After obtaining the baseline assessment, a nurse in the TB clinic will open a sealed envelope to assign the participants to either the intervention or the control groups. Subsequently, the intervention group will be given the TB educational intervention. For the post-intervention and follow‐up assessments, the participants will be asked to fill in the same questionnaire without the section on personal information.

*Study principles*. This study protocol reports based on the Study Protocol Items: Recommendations for Interventional Trials (SPIRIT) 2013 Statement [23]. It also complies with the Consolidated Standards of Reporting Trials (CONSORT) statement. Fig 3 below illustrates the Consolidated Standards of Reporting Trials (CONSORT) flowchart [24].

**Fig 3 pone.0277888.g003:**
[figure not shown]
CONSORT flow diagram of the study. Adopted from [24].

*Randomisation*. Randomisation will be maintained throughout the entire study using sealed envelopes labelled with sequential numbers. These opaque envelopes contain the treatment allocation cards prepared before the trial. An independent researcher will print out random allocation cards based on computer-generated random numbers. The treatment allocation cards will be folded several times before being placed in the envelope. The randomisation sequence will be created using online software [25], with a 1:1 allocation using random block sizes of 4 and 6.

*Allocation concealment mechanism*. A statistician will be enlisted to ensure proper allocation concealment by producing the list of allocation sequences using special block randomisation software. Every respondent will be assigned a unique code placed in a sealed opaque envelope. The research assistant will open the envelopes and assign the respondents to the intervention or control group based on the code list produced by the software. The envelopes will only be opened after the nurse has selected the respondent, obtained informed consent, and collected baseline data to avoid individual-level bias. Hence, outcome measures are collected. The intervention and control groups will be followed for an equal period of 4 months.

*Intervention*. The intervention group will be exposed to an educational intervention on TB treatment adherence. The educational material in the intervention is based on the Health Belief Model (HBM). The educational module includes two main messages of threat and efficacy aimed at enhancing or motivating the patients to engage in danger control through better adherence to TB medication [17]. In the module, the author will explain how the TB disease is acquired, the risks and consequences related to the behaviour of non-adherence, as well as the benefits of TB medication and treatment adherence.

The module for educational intervention was based on six main constructs, i.e., perceived benefit, perceived barriers, perceived susceptibility, perceived severity, perceived self-efficacy, and cue to action, all of which have been incorporated into the intervention Table 1. After the educational intervention was developed, its face and content validity were reviewed and evaluated by a respiratory specialist in the Abu Anga hospital, two public health experts from Universiti Putra Malaysia (UPM), and one public health expert from the University of Khartoum, Sudan. The experts felt that the educational materials were efficient and commented on the understandability, simplicity, and mode of delivery. After amendments, the education booklet was translated into Arabic by a professional translator to prevent any unclear phrases or grammatical errors. The intervention will be given via four sessions of a two-hour workshop in which the educational modules will be delivered in the form of PowerPoint presentation and handouts. Based on the experience of a Bangladeshi study, the intervention will take about 30 minutes for each session [17]. A discussion for 10 to 15 minutes will be conducted after the presentation of the educational module. During the discussion, the researcher will provide support to the patients with any issues related to their medication non-adherence. The researcher will also encourage the patients to perform the appropriate steps such as using a diary to monitor their medication adherence. To facilitate the discussion, the intervention group will be divided into smaller groups of 10 to 12 participants.

**Table 1 pone.0277888.t001:** Overview of the educational intervention on TB treatment adherence.

Sessions	Topics	HBM Construct	Area of target	Intervention
TB infection	Causes and transmission Symptoms and complications Does TB cause death?	Perceived susceptibility Perceived seriousness	Knowledge of TB infection	PowerPoint presentation, booklet, small group discussion
TB screening and prevention	Who is more likely to develop TB disease? Diagnosis and prevention	Perceived susceptibility Perceived seriousness	Knowledge of TB	PowerPoint presentation, booklet, small group discussion
Treatment of TB and Adherence to TB treatment	Medication for TB disease Treatment adherence Tips on how to manage poor TB adherence Barriers to medication adherence	Perceived benefits Perceived barriers Health motivation (Cues to action)	Knowledge of TB treatment Belief in TB treatment adherence	PowerPoint presentation, booklet
Goal Setting and Action Planning	Write action plans and set goals that can motivate treatment adherence. -To motivate patients to explore barriers to TB treatment adherence	Perceived benefits Perceived barriers Motivation (Cues to action Self-confidence	To motivate and increase an individual’s confidence to take action to improve their health condition.	PowerPoint presentation and booklet, handout, Participants to write their goal setting for good treatment adherence

After the educational intervention, a booklet with all the information will be offered to the participants. The booklet will include facts about TB, prevention, and screening of tuberculosis infection, treatment of tuberculosis, adherence to treatment, and TB adherence Action Plan. To avoid contamination between the intervention and the control group, the patients in the intervention group will be informed not to share the contents of the educational intervention with another group. During random allocation, participants who know someone else attending the screening will be excluded. In addition, the researchers will hold treatment sessions at different times, and the waiting time will be reduced so that participants in the intervention and control groups will not meet in the waiting room.

*Intervention group*. The educational module will be given to the participants in the intervention group to remind them about TB medication adherence. There will also be recommendations on how to manage poor medication adherence. The research team will also send monthly messages to the intervention group to remind them to adhere to their medications.

*Control group*. The control group members will receive the same routine standard treatment care as the intervention group, but will not receive any education intervention during the study. Instead, they will be provided with similar educational modules with materials and knowledge on TB treatment adherence when the study concludes.

The same set of the questionnaire at baseline, one-month, and four-month after the intervention will be administered for both groups.

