#### Outcome measures

*Intervention fidelity*. Several strategies will be employed to ensure that the educational intervention is delivered faithfully. Firstly, the intervention delivery will be provided in such a way as to preserve its consistency while at the same time making sure that the participants are encouraged and reinforced in their compliance with the intervention. Consistency in the delivery of intervention is also ensured by dividing the intervention group into smaller groups. The educational intervention will be independently conducted by the researcher for each of the smaller groups. Uniform delivery of the education intervention for all subgroups can be achieved by adhering to a strict protocol. During the sessions, instant feedback can be provided to the participants by the researcher who plays the part of an observer. Intervention fidelity is also enhanced by sending regular short text messages to keep the participants’ spirits up and to ensure that they will not lapse in TB treatment adherence.

*Participant privacy*. Honesty is particularly stressed to the participants to obtain sincere responses. The participants will be informed that the questionnaires will not contain any identifying information and they will only be tagged with a unique number for identifying them later.

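### The protocol contradicts itself on what the allocation envelope holds and who opens it, and one version has the person assigning patients work from a code list that could expose later assignments

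*Protocol article*

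**What the plan says.** Three paragraphs under Data collection describe assignment.

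- **Participant recruitment.** The clinic nurse directs eligible patients to the researcher, who explains the study. After baseline, "a nurse in the TB clinic will open a sealed envelope to assign the participants".
- **Randomisation.** The trial uses "sealed envelopes labelled with sequential numbers". Of these it says: "These opaque envelopes contain the treatment allocation cards prepared before the trial". It adds: "The treatment allocation cards will be folded several times before being placed in the envelope". An independent researcher prints the cards. The sequence is blocked, "with a 1:1 allocation using random block sizes of 4 and 6".
- **Allocation concealment mechanism.** A statistician produces the list of allocation sequences. Then: "Every respondent will be assigned a unique code placed in a sealed opaque envelope". The research assistant opens the envelopes and is to "assign the respondents to the intervention or control group based on the code list produced by the software". Envelopes are opened only once the nurse has selected the patient, taken consent and collected baseline data.

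Study design calls the trial single-blind, meaning the participants. The Discussion accepts that providers cannot be blinded.

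**The concern.** Concealment depends on two facts that the text leaves in conflict: where the arm is recorded until it is needed, and whether the person who learns it also influences who enters the trial. If the arm is on a card inside the envelope, nobody at the clinic needs a list. If the envelope holds a code, somebody must look the code up, and that person handles a document that may show more than the current patient's arm.

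Foreseen allocation could do harm here for three reasons. Providers are unblinded. Some inclusion criteria rest on judgement, such as whether a patient will stay for the whole study and can follow the intervention without help. The section on avoiding contamination adds an exclusion, at the time of random allocation, of people who know another attender. The primary outcome is self-reported adherence on the Medication Adherence Rating Scale. Staff who could see the next arm would have room to hurry, delay or discourage a patient according to expected adherence, and the resulting difference would look like an effect of the education.

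**Working it through.** The point is mainly one of reading passages against each other. The arithmetic at the end only sizes what a list could add.

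**1. The accounts side by side**

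| Element | One account | Other account |
|---|---|---|
| Envelope content | Allocation card (Randomisation) | Unique code (Allocation concealment mechanism) |
| Where the arm is read | On the card (implied) | From the software's code list |
| Who opens | Nurse in the TB clinic (Participant recruitment) | Research assistant (Allocation concealment mechanism) |
| Who selects and consents | Nurse refers, researcher explains the study (Participant recruitment) | Nurse selects and obtains consent (Allocation concealment mechanism) |

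The independent researcher who prints cards and the statistician who produces the list could be two steps of one process. I do not count that as a contradiction, but the text should say who holds the list.

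**2. Can the accounts be merged?**

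- If the card shows the arm, opening it settles the assignment and the lookup step is redundant.
- If the card shows only a code, the two statements of content agree, but a list is then needed each time a patient is assigned.
- Neither reading resolves who opens the envelope. Combining the nurse as opener with the nurse as selector puts enrolment and assignment in the same role.

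**3. What the timing rule protects**

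Opening after selection, consent and baseline protects information that is inside the envelope. Under the code version the arm is on the list, so the rule does not reach it.

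**4. When the list would expose the sequence**

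Three conditions are needed: (a) the list covers future assignments; (b) its codes run in envelope order, or the order can be worked out; (c) someone who influences recruitment can see it. The documents state none of these. If (b) fails, the sealed envelope still hides which code comes next.

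**5. Size of the exposure**

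Input from the Randomisation paragraph: 1:1 allocation, blocks of 4 and 6. Assumptions: both sizes equally likely, and the guesser knows every past assignment in order. The guesser names whichever arm is behind and tosses a coin when the arms are level. In a block of size 2m the expected number of correct guesses is

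m + ½ × (4^m / C(2m, m) − 1).

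- Block of 4 (m = 2): 2 + ½ × (16/6 − 1) = 2.833
- Block of 6 (m = 3): 3 + ½ × (64/20 − 1) = 4.100
- Share correct: (2.833 + 4.100) / (4 + 6) = 0.693

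Simulated sequences of 376, the total in the Sample size section, also give 0.693. The scale is therefore:

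| What the person knows | Chance of naming the next arm |
|---|---|
| Nothing about the sequence | 50% |
| All past assignments, no list | about 69% |
| Complete list in envelope order | 100% |

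Whoever opens every envelope learns all past assignments under either mechanism. That is a reason to keep the opener out of selection and consent whichever version is kept.

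**The case against.** The strongest reply is that this is loose wording in a condensed article. The card may carry the code, and the mention of the code list may simply name where the allocation came from. A lookup list can be sorted by code with no relation to envelope order. The concealment paragraph, taken alone, separates the nurse who enrols from the research assistant who assigns. Custody of the list is something an article commonly leaves to the full protocol. Baseline is collected before the envelope is opened, and the Statistical analysis section plans multivariable adjustment, which could absorb part of any imbalance in measured factors.

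Much of this stands. A reader might infer that the whole forthcoming sequence can be read at the clinic and that the envelopes conceal nothing. The documents do not support that. One paragraph does put cards in the envelopes, and nothing says that the list is on site, complete, in envelope order or visible to anyone who recruits. Silence on custody would not be a finding by itself.

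The 69% is also a ceiling for someone without the list. The researcher, who both explains the study and teaches ("The educational intervention will be independently conducted by the researcher for each of the smaller groups"), may learn arms late, because teaching is in groups of 10 to 12. Random blocks of 4 and 6 are an accepted choice; preferring larger ones is a matter of taste.

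What does not fall is the conflict in the printed text. It gives two envelope contents and two openers, and a literal reading of one version makes a list part of the assignment step. Adjustment cannot be relied on to repair selection on factors that are not measured.

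**Conclusion.** The contradiction is established from the text alone: card or code, nurse or research assistant. It matters because a site following the code-and-list version would have the assigning person use a document that could reveal later assignments, and the protocol's timing rule would not prevent that.

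The exposure is conditional. It reaches 100% only if the list is complete, follows envelope order and is seen by someone who influences enrolment. Against that stand 50% for someone who knows nothing and about 69% for someone who knows all past assignments, the latter assuming equally likely block sizes.

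I attach no figure to the resulting bias or false-positive rate. That would need a split of patients by prognosis and a share of patients steered, and the documents give neither. The point should be settled before enrolment, because bias from foreseen allocation cannot be reliably corrected in the analysis.

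**What to change.** Reconcile the Participant recruitment, Randomisation and Allocation concealment mechanism paragraphs into one procedure:

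1. Delete the code-and-list step. Keep the allocation card itself inside each sequentially numbered opaque envelope.
2. Name one opener, who neither selects nor consents patients, and use that role in all three paragraphs.
3. State that the sequence list stays with the independent person who generated it and is not seen by anyone who recruits, consents, assigns or teaches.
4. Open envelopes in strict number order, with the participant number and date written on the envelope first.

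This uses the envelopes, software and independent list-maker already planned. The cost is protocol wording and a site instruction, with no effect on sample size or analysis.

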### Sample size

The sample size is calculated using the standard sample size estimate for an individually randomised design. Sample size will be determined according to the primary dependent variable (TB treatment adherence). The formula to calculate the difference between two population proportions will be used (power = 0.80, alpha = 0.05 two‐sided, P_1_ = estimated proportion (larger) P1 = 0.82, P_2_ = estimated proportion (smaller) P2 = 0.69) [22].

$$N=\frac{\{1.96\sqrt{2\times 0.33(1-0.33)}+0.842\sqrt{0.82(1-0.82)+o69(1-0.69)}{\}}^{2}}{{\left(0.82-0.69\right)}^{2}}.$$

N = 171 for each group.

By taking into account a 10% attrition rate, a total sample size of 188 (171 + 17 = 188) participants will be required for each group, giving a total sample size of 376 participants.

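### The intervention arm is taught in workshop groups of 10 to 12, but the sample size assumes independent patients and no stated analysis accounts for the workshop group

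*Protocol article*

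**What the plan says.** **Randomisation.** The Randomisation paragraph allocates individual patients 1:1 in blocks of 4 and 6.

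**Delivery.** In the Intervention text, "the intervention group will be divided into smaller groups of 10 to 12 participants" so that discussion is easier. A discussion of 10 to 15 minutes follows the presentation, and Table 1 lists small-group discussion as a component. The Intervention fidelity paragraph says that the researcher runs the intervention separately for each small group, under a strict protocol. The Control group paragraph gives controls no education until the study ends.

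**Size.** The Sample size section states: "The sample size is calculated using the standard sample size estimate for an individually randomised design". Its inputs are "alpha = 0.05 two‐sided", power 0.80, and proportions 0.82 and 0.69. It reports "N = 171 for each group", then 188 per group with 10% attrition and 376 in total. It mentions no ICC or design effect.

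**Analysis.** The Statistical analysis section names chi-square and t-tests, multivariable regression, Cochran's Q, repeated-measures ANOVA, and generalised estimating equations (GEE) for the group effect and its interaction with time. The workshop group appears in none of them.

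**Heading.** The recruitment text under Data collection is headed "Cluster randomized trial flow".

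**The concern.** Individual randomisation followed by group teaching in one arm is a partially nested design. Members of a workshop share a session, a discussion of their own adherence problems, and peers. The primary outcome is self-reported adherence on a scale that includes attitude items, and a shared discussion could plausibly move several members' answers together. Controls have no such grouping.

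If that correlation is positive, 171 intervention patients carry less information than 171 independent ones. An analysis that ignores the workshop then understates the standard error of the treatment difference and rejects more often than its nominal 5%. An analysis that respects the workshop has less power than stated. The first error favours declaring the intervention effective.

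The matter is also time-sensitive. The article mentions no workshop identifier, and the Participant privacy paragraph says questionnaires carry only a unique patient number. If the workshop is not recorded at delivery, it may not be recoverable.

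**Working it through.** **Inputs from the Sample size section:** p1 = 0.82, p2 = 0.69, difference d = 0.13, two-sided alpha 0.05 (z = 1.96), power 0.80 (z = 0.842), n = 171 per arm before attrition. **From the Intervention text:** workshop size m = 10 to 12, with 11 taken as the midpoint. **Assumed, because the article gives none:** ICC of 0, 0.01, 0.02 or 0.05.

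**Step 1: reproduce the plan's figure.** The pooled proportion is (0.82 + 0.69)/2 = 0.755.

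n = {1.96·√(2 × 0.755 × 0.245) + 0.842·√(0.82 × 0.18 + 0.69 × 0.31)}² / 0.13² = 170.7, so 171.

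Power at 171 per arm is 80.1%. The stated size is therefore the independent-patient figure, with no allowance for grouping. (The printed formula shows 0.33 in place of the pooled proportion and would give 194. The stated 171 comes from 0.755.)

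**Step 2: number of workshops.** 188/12 = 15.7 and 188/10 = 18.8, so about 16 to 19.

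**Step 3: inflate the variance in the intervention arm only.** The design effect is DE = 1 + (m − 1) × ICC in the intervention arm and 1 in the control arm.

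- Null standard error: se0 = √{0.755 × 0.245 × (DE + 1)/n}
- Alternative standard error: se1 = √{(0.82 × 0.18 × DE + 0.69 × 0.31)/n}
- Power = Φ{(d − 1.96·se0)/se1}
- Ratio of true to independence standard error under the null: r = √{(DE + 1)/2}
- Type I error if clustering is ignored: 2·{1 − Φ(1.96/r)}

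Worked case, m = 11 and ICC 0.05: DE = 1 + 10 × 0.05 = 1.5; se0 = √(0.184975 × 2.5/171) = 0.0520; se1 = √{(0.1476 × 1.5 + 0.2139)/171} = 0.0505; power = Φ{(0.13 − 0.1019)/0.0505} = Φ(0.556) = 71.1%. For the type I error, r = √1.25 = 1.118 and 2·{1 − Φ(1.753)} = 8.0%.

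| ICC (assumed) | DE, intervention arm | SE ratio r | Type I error, clustering ignored | Power at 171 per arm, clustering respected | n per arm for 80% power, before attrition |
|---|---|---|---|---|---|
| 0 | 1.0 | 1.00 | 5.0% | 80.1% | 171 |
| 0.01 | 1.1 | 1.02 | 5.6% | 78.2% | 179 |
| 0.02 | 1.2 | 1.05 | 6.2% | 76.4% | 187 |
| 0.05 | 1.5 | 1.12 | 8.0% | 71.1% | 211 |

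**Step 4: sensitivity to workshop size.** At ICC 0.05, power is 72.0% for m = 10 and 70.3% for m = 12. Attrition of 10% would leave about 10 of 11 in each workshop (11 × 0.9 = 9.9), so the m = 10 figure is a fair alternative.

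**Step 5: the other total.** The abstract gives 146 patients, or 73 per arm. There the same formula gives 44.6% power with no clustering and 36.8% at ICC 0.05. The table applies only to the total of 376.

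**The case against.** **The effect is conditional, and the design limits it.** This stands. The harm needs a positive workshop ICC, and the article gives none. One researcher teaches every group under a strict protocol, which removes most facilitator differences. Participants who know someone else attending are excluded. Contact is short, and adherence is measured one and four months later. At ICC 0.01 the loss is about 2 power points. None of this removes the shared discussion, which is an intended component, so a zero ICC cannot be taken for granted either.

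**Type I error is inflated only under a particular null.** This also stands. If the workshop changes nobody's outcome, attending together creates no correlation. Correlation from the recruitment period could be shared by controls enrolled at the same time. The tabulated type I figures apply when workshops raise outcomes in some groups and lower them in others, averaging to no effect.

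**A fuller plan may already cluster on workshop.** A reader might infer that the GEE handles only repeated measures within a patient. The article describes it over time but names no cluster variable, correlation structure or variance estimator, and those details commonly sit in an analysis plan that is not shown. So it cannot be said that the GEE ignores workshops, only that no stated analysis is said to account for them. This does not rescue the sample size, which the article fixes on independent patients.

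**The power figures are not for the planned GEE.** Correct. They describe a single-time comparison of two proportions, the only basis on which the article states power. Baseline and repeated measures could change precision.

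**The heading is a labelling slip.** Agreed. A reader might take it to mean that clusters are randomised. The Sample size section and the Randomisation paragraph show individual allocation, so the heading is no evidence about workshop correlation.

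**Conclusion.** The point holds in conditional form. The intervention arm is grouped after randomisation, the sample size makes no allowance for that, and no stated analysis is said to account for it. If the within-workshop ICC lies between 0.01 and 0.05, the 80% power for the planned two-proportion comparison is really about 78% to 71%, and an analysis ignoring workshops would run at about 5.6% to 8.0% instead of 5%. Near zero ICC the effect is trivial.

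These figures rest on an assumed ICC, 11 patients per workshop, 171 analysable per arm, clustering in the intervention arm only, and the total of 376. The conflict between 376 and the abstract's 146 is a separate matter with a much larger effect on power.

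A reader might go further and conclude that the standard errors are certainly too small, or quote the results at ICC 0.10 (63% power, 11% type I error). The documents support neither: they give no ICC and no reason to expect one that high. Applying the design effect to both arms would overcorrect, since controls are ungrouped.

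The plan should be changed, because the remedy is cheap and depends on data that must be captured at delivery. The point does not invalidate the design.

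**What to change.** 1. **Record the workshop number** for each intervention patient when the session is delivered, and decide beforehand how to code an intervention patient who attends none.
2. **GEE:** use the workshop as the top-level cluster in the intervention arm and each control patient as a cluster of one, with repeated visits nested within patient. Add a small-sample variance correction, because only about 16 to 19 workshops are expected, and check that the chosen software provides it.
3. **If a mixed model is used instead:** include a patient random effect for the repeated visits, plus a workshop effect in the intervention arm at post-baseline visits only. A workshop intercept alone does not cover repeated measures. Applied at every visit, it would also impose workshop correlation on the baseline, which is collected before allocation.
4. **Sample size section:** restate power over an assumed ICC range, once the total is settled.
5. **Heading:** change the cluster-randomised label under Data collection to individually randomised.

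The cost is one extra variable, slightly wider intervals and a lower stated power. If the investigators prefer to keep 80% power, the same formula needs 179 to 211 per arm before attrition for ICC 0.01 to 0.05, against 171 now.

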### Eligibility criteria

The inclusion criteria are (1) Patients on a full TB treatment course for 1 or 2 months before the study date; (2) TB patients who can give informed consent physically and mentally and who can abide by the provided intervention with no difficulty or needing assistance; (3) Patients who can commit to the entire course of the study; (4) Patients aged 18 years or older.

The exclusion criteria are (1) Patients with a history of severe and uncontrolled psychiatric disorders; (2) Patients who are unable to read and write in Arabic; (3) TB patients not on a full TB treatment course.

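### The acquaintance exclusion is placed at random allocation with no statement that it precedes envelope opening, and two sections name different envelope openers

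*Protocol article*

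**What the plan says.** **The exclusion.** The paragraph on avoiding contamination, after Table 1 of the protocol article, says: "During random allocation, participants who know someone else attending the screening will be excluded". The Eligibility criteria section lists three exclusions. It begins "The exclusion criteria are (1) Patients with a history of severe and uncontrolled psychiatric disorders" and goes on to inability to read and write Arabic and not being on a full treatment course. Knowing another attendee is not on the list.

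**When allocation happens.** Under Allocation concealment mechanism: "The envelopes will only be opened after the nurse has selected the respondent, obtained informed consent, and collected baseline data". Participant recruitment gives the same order, with assignment following the baseline assessment.

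**Who opens the envelope.** Participant recruitment: "a nurse in the TB clinic will open a sealed envelope to assign the participants". Allocation concealment mechanism: "The research assistant will open the envelopes and assign the respondents to the intervention or control group".

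**Who recruits.** In Participant recruitment, "the nurse will direct the TB patients who fulfil the inclusion criteria to the researcher", and then "The researcher then explains the purpose and benefits of this study". In Allocation concealment mechanism it is the nurse who selects, consents and collects baseline data.

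**Safeguards.** The Randomisation and Allocation concealment paragraphs specify sealed, opaque, sequentially numbered envelopes. The folded cards are prepared beforehand by someone independent from a computer-generated 1:1 sequence in random blocks of 4 and 6.

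**Analysis set.** The Statistical analysis section invokes intention-to-treat as its way of managing missing data. It does not say how a patient excluded at allocation is counted.

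**The concern.** An exclusion is harmless to comparability if it is decided before anyone can know the patient's assignment. It is not harmless if it can be decided afterwards. This rule is tied to the allocation step and needs a judgement about what counts as knowing someone. Its purpose is to prevent contamination, and acquaintance matters for that mainly when the two people are in different arms. Staff who follow the text as it stands thus have a reason to look at the assignment before deciding whether to exclude. Patients lost in that way could differ between arms, and no later adjustment reliably repairs it.

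The disagreement over the opener bears on the same safeguard. Concealment is strongest when the person who opens envelopes, and so accumulates knowledge of past assignments, has no say in who enters next. With two incompatible descriptions, and nurses given recruitment tasks in both sections, the protocol does not secure that separation.

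**Working it through.** **1. The order of events.** Both sections that describe the procedure give selection, then consent, then baseline data, then envelope. The acquaintance rule is tied to the last step. The text leaves two readings open:

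- The check is made just before the envelope is opened. No assignment is yet known for that patient, and the fault is only an unlisted criterion applied late.
- The check is made with or after opening. The patient has been randomised and is then removed.

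No sentence chooses between them.

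**2. The roles, side by side.**

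| Task | Participant recruitment | Allocation concealment mechanism |
|---|---|---|
| Refers or selects patients | the nurse refers | the nurse selects |
| Explains the study or obtains consent | the researcher explains | the nurse obtains consent |
| Opens the envelope | a TB clinic nurse | the research assistant |

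The last row is a direct contradiction.

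**3. Size of bias if patients were removed after assignment.** Inputs from the Sample size section: adherence 0.69 (lower) and 0.82 (higher), a planned difference of 0.13. These proportions underlie the stated 171 per group. With their mean, 0.755, {1.96√(2×0.755×0.245) + 0.842√(0.82×0.18 + 0.69×0.31)}² / 0.13² = 170.7, rounded up to 171. The printed formula shows 0.33 where 0.755 is needed to reach 171; that is a separate matter and does not affect this point.

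Assume no true effect, 0.69 in both arms, and remove a fraction r from one arm only. If those removed have adherence q, that arm then shows (0.69 − r·q)/(1 − r). The documents give neither r nor q, so both are assumptions:

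| Adherence of those removed | r = 5% | r = 10% |
|---|---|---|
| q = 0.69 (unrelated to adherence) | 0.690 (0) | 0.690 (0) |
| q = 0.50 | 0.665/0.95 = 0.700 (+1.0 point) | 0.640/0.90 = 0.711 (+2.1 points) |
| q = 0 (all non-adherent) | 0.69/0.95 = 0.726 (+3.6 points) | 0.69/0.90 = 0.767 (+7.7 points) |

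The last row is the worst case for inflating that arm. If the same kind of patient were removed equally from both arms, the difference would again be zero. If the removals were in the control arm, the sign would reverse.

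**4. Predictability from past assignments.** Suppose someone sees every past assignment and always guesses the arm that is behind, tossing a coin when the arms are level. In a permuted block of size 2m the expected number of correct guesses is m + ½[2^(2m)/C(2m, m) − 1].

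- Block of 4: 2 + ½(16/6 − 1) = 2.833, or 70.8%.
- Block of 6: 3 + ½(64/20 − 1) = 4.1, or 68.3%.
- Both sizes equally frequent: (2.833 + 4.1)/10 = 69.3%, against 50% by chance.

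A simulation of 376 allocations gave the same 0.693. The strategy uses only the running count, so not knowing the block size does not lower it. It does require sight of all past assignments.

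**The case against.** Several stronger readings are tempting, and the documents do not support them.

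- *That the plan excludes patients after randomisation.* A reader might infer this from the timing phrase. But the sentence refers to people attending the screening, so a check before assignment is also a natural reading, and it does not say who applies the rule. Removal after assignment is possible, not established.
- *That the intention-to-treat statement is already contradicted.* That statement concerns missing data. A conflict arises only if a patient is dropped after the envelope is opened.
- *That the nurse who recruits also opens the envelopes.* This joins two sections. Participant recruitment says only that a clinic nurse opens and does not identify this person with the referring nurse. The nurse who selects and consents appears in the other section, where the research assistant opens.
- *That the bias is several points.* The trigger is acquaintance, not adherence, and adherence after the intervention is measured one and four months later. Nothing in the documents ties removals to one arm or to non-adherent patients.

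The envelope safeguards also deserve credit. If followed, nobody can read a patient's assignment when selecting that patient. What stands against the objection is narrower. Good envelopes do not stop a removal once the envelope is open, and they do not stop inference from past assignments. The acquaintance rule and the two openers are also statements in the text, not details left to a fuller document.

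**Conclusion.** The point holds as an unlisted exclusion whose timing relative to envelope opening is left open, together with a contradiction over who opens the envelope. Removal at or after assignment is not ruled out, and separation of recruitment from allocation is not secured.

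The size of any bias cannot be fixed from the documents. The range in the table starts at zero, and its upper end needs both one-sided removal and universal non-adherence among those removed. The 69% figure is sound for someone who sees all past assignments, but no section gives one person both that view and control over who enters. The possible removal of patients is the main ground for changing the text; prediction of the next assignment is secondary. Both should be settled before the first patient is randomised.

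**What to change.** 1. Move the acquaintance rule into the Eligibility criteria, to be applied and logged at screening, before any envelope is taken. Delete the reference to random allocation in the contamination paragraph.
2. State that everyone whose envelope has been opened stays in the trial and is analysed in the assigned group.
3. Reconcile Participant recruitment with Allocation concealment mechanism so that one role opens all envelopes. The research assistant, already in the plan, can do this, provided that this person takes no part in selection, consent or baseline collection.

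The cost is protocol wording and a few more patients screened out before randomisation. No extra staff are needed. One limit remains: the researcher who explains the study to patients also delivers the sessions (Intervention fidelity) and so learns past allocations whoever opens the envelopes. Naming the opener settles the contradiction but does not by itself remove that predictability.
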